### Study measures

Almost all data being gathered during the trial are self-reported data that will be collected via an online survey program (https://www.qualtrics.com). In addition, one semi-structured telephone interview will be conducted 12 months after baseline to assess relapse. Participants will be asked to report demographical data including gender, age, marital and employment status, ethnicity and education, as well as the information about the past course of BD, at baseline. The primary outcome is well-being and secondary outcomes include personal recovery, social role participation and symptoms of depression, mania and anxiety. Additionally, processes of positive emotions, self-compassion and positive relationships are assessed and economic outcomes are used to calculate the cost-effectivness. An overview of the study measures at the different time points can be found in Table 2*.*

**Table 2 Tab2:** Overview of study parameters and measurement points

Questionnaire	Outcome	Screening	T0	T1	T2	T3	T4
			Pre-test	Mid-treatment^a^	Post-test	Follow-up^b^	Follow-up^c^
CGI-BP^d^	Global illness severity	X					
MINI	Diagnosis BD	X					
MHC-SF	Well-being	X	X	X	X	X	X
QPR	Personal recovery		X		X	X	X
s-SRPQ	Social participation		X		X	X	X
QIDS-SR	Depressive symptoms		X		X	X	X
ASRM	Manic symptoms		X		X	X	X
HADS-A	Anxiety symptoms		X		X	X	X
PANAS	Positive emotions		X	X	X		
SCS-SF	Self-compassion		X	X	X		
SPWB	Positive relationships		X	X	X		
RPA	Dampening of positive affect		X	X	X		
Telephone interviews	Relapse						X
EQ-5D-5 L	Quality of Life		X				X
TiC-P	Costs associated with psychiatric illness		X				X
Socio- demographics	Gender, age, education, marital status, living situation, ethnicity		X				

^a^4 weeks after intervention begin

^b^6 months after baseline

^c^12 months after baseline

^d^clinician reported

#### Global illness severity

To screen for the presence of depressive and (hypo)manic symptoms and determine eligibility of possible participants, the Clinical Global Impression – Bipolar (CGI-BP; [59]) scale will be used. This scale comprises three different measures, including severity of depressive and (hypo)manic symptoms, change from preceding phases and change from worst phase of illness. For this study, only the measure assessing the severity of symptoms will be used ranging from 1 (normal, not ill) to 7 (very severely ill). The CGI-BP showed excellent interrater reliability in prior studies [59].

#### Well-being

The Mental Health Continuum – Short Form (MHC-SF) is a comprehensive well-validated measure of well-being [58]. The MHC-SF measures three dimensions of well-being: 1) emotional well-being (three items), defined in terms of the presence of positive feelings, the absence of negative feelings and satisfaction with life; 2) psychological well-being (six items), defined in terms of positive functioning in individual life in terms of e.g. self-acceptance, personal goals, positive relationships, and environmental mastery; 3) social well-being (five items), defined in terms of positive functioning in social life in terms of e.g. social integration and social contribution. Participants rate the frequency of feelings in the last week. A total score can be created by summing all 14 items, where higher scores indicate better positive well-being. The Dutch version of the MHC-SF showed high internal consistency for total scores (*α* = 0.89) and for the subscales *emotional* (*α* = 0.83) and *psychological well-being* (*α* = 0.83) and adequate reliability for the subscale *social well-being* (*α* = 0.74) and correlates well with corresponding aspects of well-being and functioning, showing convergent validity [58].

#### Personal recovery

To comprehensively assess personal recovery, the 15-item version of the Questionnaire about the Process of Recovery is used (QPR; [60, 61]).The scale aims to assess personal recovery in the last 7 days (e.g. “I feel better about myself” or “I can actively engage with life”), with items being scored on a 5-point Likert scale, ranging from 0 to (*disagree strongly*) to 4 (*agree strongly*) and higher scores being indicative of recovery. The internal consistency of the 15-item version has been found to be high (*α* = 0.89) in a sample of psychotic patients [62] and in a group of individuals with a schizophrenia spectrum diagnosis (*α* = 0.93) [61]. For this study, the QPR has been translated into Dutch via forward and backward translation.

#### Social role participation

The Social Role Participation Questionnaire (SRPQ; [63]) assesses social role participation. For this study, the short version of the questionnaire (s-SRPQ; [64]) will be used, which consists of 12 items, measuring the influence of (psychological) health in the past on six social roles (e.g. intimate relationship or employment) along two dimensions: (1) satisfaction with role performance and (2) experienced physical / psychological difficulty. Items are scored on a 5-point Likert Scale, reaching from 0 (*not satisfied at all / no difficulties at all*) to 4 (*very much satisfied / not possible*), with higher scores indicating more satisfaction respectively more experienced difficulties with a social role. The psychometric qualities of the Dutch s-SRPQ were found to be good for both subscales *(α* = 0.86) [64].

#### Depressive symptoms

The self-report version of the Quick Inventory of Depressive Symptomatology (QIDS-SR) [65, 66] assesses depressive symptoms in the past on 16 items. The scale requires individuals to rate different depression symptoms, such as sad mood, concentration, suicidal ideation, general interest, energy/fatigue, sleep, appetite and weight. Items are scored on a 4-point Likert Scale with different answering categories. A total score can be obtained by summing all items, with higher scores indicating more depressive symptomatology. The QIDS-SR has shown to be internally consistent (*α* = 0.86) [65].

#### Manic symptoms

Current manic symptoms are measured using the Altman Self-Rating Mania Scale (ASRM) [67]. The scale consists of five statements that represent different manic symptoms, including feeling happier, self-confident and talkative than normal. All five items are rated on a 5-point Likert scale with different answering categories. A total score can be obtained by summing all items, with higher scores indicating more manic symptomatology. The ASRM has high test-retest reliability [67], has been shown to be sensitive to changes of clinical states [68] and to predict related measures in non-clinical student samples [69].

#### Anxiety symptoms

The anxiety subscale of the Hospital Anxiety and Depression Scale (HADS-A; [70]) is used to assess anxious symptomatology. The HADS-A aims to measure anxiety symptoms in 7 items. Participants rate the frequency of symptoms (e.g. “Worrying thoughts go through my mind”) on a scale ranging from 0 (“not at all”) to 3 (“very often”) and higher scores indicate higher anxiety symptoms. The Dutch version of the HADS-A [71] has been shown good internal consistency in a sample from the general population (*α* = 0.84) and in a sample of psychiatric outpatients (*α* = 0.81).

#### Positive emotions

The Positive and Negative Affect Schedule (PANAS) [72] measures current emotions on two different dimensions: (1) positive and (2) negative affect and includes 20 items describing emotional states (e.g. “*active*” or “*anxious*”). Participants can score those states on a 5-point Likert scale, representing the extent to which they experience an affect at this moment or have experienced in the past week, reaching from 1 (*very slightly or not at all*) to 5 (*extremely*). The scores can be summed up to gain scores for positive and negative affect respectively, with higher scores indicating higher affectivity. For this study, the Dutch version of the PANAS and only the positive affect subscale will be used, which showed acceptable reliability (*α* = .79) [73].

#### Self-compassion

The Self-Compassion Scale – Short Form (SCS-SF) [74, 75] measures the process of self-compassion on six dimensions: (1) self-kindness, (2) self-judgment, (3) common humanity, (4) isolation, (5) mindfulness and (6) over-identification and contains 12 items (e.g., “*When I fail at something important to me I become consumed by feelings of inadequacy”*). Each dimension is assessed by two items, which are scored on a 7-point response scale ranging from 1 (*almost never*) to 7 (*almost always*), representing the extent to which an individual experiences certain aspects of self-compassion. Higher scores indicate an increased degree of self-compassion. Reliability of the total Dutch SCS-SF was shown to be good (*α* = .87). Solely total scores of the SCS-SF will be used for further analyses, since the psychometric properties of the subscales were questionable [74].

#### Positive relationships

The process of positive relationships is assessed using the Scales of Psychological Well-Being (SPWB; [76]), which assesses psychological well-being on six different dimensions (e.g. environmental mastery, self-acceptance). For this study, the subscale *positive relations* will be used measuring the extent to which an individual experiences meaningful intrapersonal relationships with other people (e.g. “*People would describe me as a giving person, willing to share my time with others*”). Items are scored on a scale ranging from 1 (*strongly disagree*) to 6 (*strongly agree*) with higher scores indicating more positive relations with others. Different versions of the SPWB exist within literature, differing in number of items per subscale (reaching from 3 items to 20 items per subscale). For feasibility reasons and since the short version of this subscale (3-items) showed unacceptable internal consistency (*α* = .44–.52), we decided to use the 9-item version of the *positive relationship* subscale, which showed acceptable internal consistency in two previous studies (*α* = .77) in samples of psychology students and professionals from a divers occupation background [77].

#### Dampening of positive affect

To assess the process of dampening the Responses to Positive Affect Questionnaire (RPA; [78, 79]) is used, which consists of 17 items and measures cognitive responses to positive affective states. Respondents rate the items on a 4-point Likert scale, ranging from 1 (*almost never*) to 4 (*almost always*). For this study, only the subscale *dampening* is used (e.g., “I don’t deserve this”), which assesses the tendency to cognitively avoid or suppress positive emotions (eight items). Scores of the scales are calculated by summing up the scores on the items. The Dutch version, which is used in this study, showed satisfactory internal consistency (*α* = 0.80) for the dampening subscale [78].

#### Relapse

Semi-structured telephone interviews will be performed with people of both the intervention and control group. Goal of the interviews is to retrospectively illustrate the mood development in the time after the intervention and to capture depressive or manic mood swings with the Life Chart Method [80]. The interviews allow to graphically score severity of mood swings, the time they appeared (i.e., in which month) and which type of mood swings appeared (e.g., rapid cycling). The interview has been applied successfully in a previous study to measure relapse [14].

### Economic measures

#### Quality of life

The EQ-5D-5 L [81] is a quality of life measure consisting of five items representing five dimensions (mobility, self-care, usual activities, pain/discomfort and anxiety/ depression). For each dimension/item, individuals rate the extent of problems ranging from ‘no problems’ to ‘extreme problems’.

#### Costs associated with psychiatric illness

The Trimbos and iMTA questionnaire on costs associated with psychiatric illness (TiC-P) [82] is a measure of health care utilization and production loss in patients with psychiatric disorders. Items are generic and not related to a specific psychiatric disease. A first part of the TiC-P includes 9 structured no/yes items on medical consumption (e.g. contact with specific mental health care providers). A second part (13 items) consists of the Short Form-Health and Labour Questionnaire, a generic instrument to collect data on productivity losses due to health problems (e.g. absence from work).

### Data collection, management and storage

Data will be handled confidentially in accordance with the Dutch Personal Data Protection Act. For the purpose of this study, a data management plan has been created with DMPonline (https://dmponline.dcc.ac.uk). Details of data management procedures can be requested from the first author of this manuscript. Quality checks, including double data entry and range check for data values will be performed by the first author (JK) and an additional researcher. Personal data will be coded with an individual ID-code, which is not relatable to the participant. All collected data will be stored in a file containing only the identification code. The coded research data will be stored at the BMS Datalab of the University of Twente for a period of 15 years. In this time period, data is accessible to other researchers. After the period of 15 years, data will be stored in long time storage at Data Archiving and Networked Service by the Royal Dutch Academy of Sciences. Participants who want to be informed about their personal data or who want their data deleted can send a request to the principal investigator.

### Study integrity

The study protocol has been designed in accordance with the SPIRIT STATEMENT [83] and the study has been approved by the Medical Ethical Committee Twente (Proposal No: NL62997.044.17). The study will be carried out according to the principles of the Declaration of Helsinki (64th WMA General Assembly, Fortaleza, Brazil, October 2013) and the Medical Research Involving Human Subjects Act (WMO).

### Statistical methods

#### Power calculation

The sample size calculation for this trial is conservatively based on the ability to detect at least a moderate effect of Cohen’s *d* = 0.60 in the post-hoc tests on the primary outcome (well-being) at post-intervention (T1). For a two-sided independent t-test with 80% power and *α* = 0.05, this requires 45 patients for both treatment groups. Taking a maximum drop-out rate of 20% into account, a total of 112 patients will need to be included for the per-protocol analysis.

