#### Statistical analyses

Analyses will be done on both intention to treat (ITT) and per-protocol basis. The primary ITT analyses will be performed using linear mixed modelling (LMM) that adequately deals with missing at random data and the nested structure of repeated-measures data. LMMs with time, treatment and time-by-treatment interactions will be performed to test the effectiveness of the intervention in improving continuous primary and secondary outcomes of well-being, personal recovery, psychopathology, sef-compassion, positive relationships and dampening. Post-hoc independent t-tests with Holm-Bonferroni correction will be performed to test for significant between-group differences at all time-points. Based on estimated marginal means and corresponding standard errors from the LMM models, between-group standardized effect sizes will additionally be expressed as Cohen’s d with 95% confidence intervals (CI). Binary relapse data from the interviews will be analyzed with Kaplan Meyer survival estimates to compare the time to relapse and relapse rates between the intervention and control group. Differences in the proportion of relapsed patients and predictors of relapse will be additionally examined using generalized (binary) LMMs with post-hoc chi-square tests and relative risks (RR) with 95% CI to examine the significance and magnitude of differences at each follow-up point. Moderation and mediation analyses will be conducted to explore possible working mechanisms of the interventions. To calculate the cost-effectiveness of the intervention, quality adjusted life years (QALYs) will be taken into account as primary utility measure. QALYs will be calculated from the EQ-5D-5 L. The incremental cost-utility ratio (ICUR) will be calculated by dividing the difference in costs calculated from the TiC-P by the difference in the QALYs produced by the two groups. The ICUR is expressed as costs per QALY gained.

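### The 80% power is for an uncorrected t-test, but the plan Holm-corrects that test across time-points, so its power at 45 per arm is below 80%

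*Protocol article*

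**What the plan says.** The Power calculation section bases the sample size on "the ability to detect at least a moderate effect of Cohen’s *d* = 0.60 in the post-hoc tests", places that effect "in the post-hoc tests on the primary outcome (well-being) at post-intervention (T1"), and describes this choice as conservative. The test is specified as follows: "For a two-sided independent t-test with 80% power". The significance level and result follow: "80% power and *α* = 0.05, this requires 45 patients for both treatment groups". After a 20% drop-out allowance, "a total of 112 patients will need to be included for the per-protocol analysis".

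The Statistical analyses section says of the tests on which the size is based: "Post-hoc independent t-tests with Holm-Bonferroni correction will be performed to test for significant between-group differences at all time-points". It also says "The primary ITT analyses will be performed using linear mixed modelling (LMM"), with time, treatment and their interaction.

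The Study design section lists five measurement points, T0 to T4. Table 2 shows the well-being questionnaire (MHC-SF) at all five. Study design defines T1 as mid-treatment and T2 as the post measurement, whereas the power section labels post-intervention as T1.

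**The concern.** Both sections speak of post-hoc independent t-tests between groups, so they describe the same test. One gives its power at the full 0.05. The other subjects it to a multiplicity correction and exempts no time-point. Under Holm, the smallest p-value in a family of k tests is judged at 0.05/k, the next at 0.05/(k − 1), and so on. The post-intervention comparison reaches the full 0.05 only if every other test in the family has already been rejected. The power statement makes no allowance for this.

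At stake is how a null result at post-intervention would be read. The Background promises an adequately powered trial and criticises earlier studies as underpowered. If the corrected test misses a true d = 0.60 in roughly three to four trials out of ten, rather than two, a non-significant corrected p-value is weaker evidence against benefit than the stated 80% suggests.

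**Working it through.** **Inputs.** From the Power calculation section: d = 0.60, two-sided α = 0.05, power 80%, 45 per arm, 20% drop-out, 112 in total. From the Statistical analyses section: Holm-Bonferroni over all time-points. From Study design and Table 2: MHC-SF at T0, T1, T2, T3 and T4.

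**Step 1: reproduce the plan's figure.** For a two-sample t-test with n per arm, the noncentrality is d·√(n/2) on 2n − 2 degrees of freedom. Solving for 80% power at α = 0.05 gives n = 44.6, hence 45. At n = 45 the noncentrality is 0.60 × √22.5 = 2.846 on 88 df, the critical value is 1.987 and power is 80.4%. For drop-out, 90/0.8 = 112.5, so 112 is right to within rounding. The stated figures hold for one uncorrected test.

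**Step 2: the same test at the first Holm step, α = 0.05/k.** The noncentrality stays at 2.846.

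| Family | k | α at first step | Critical t (88 df) | Power at 45 per arm | d detectable at 80% power |
|---|---|---|---|---|---|
| uncorrected | 1 | 0.05 | 1.987 | 80.4% | 0.60 |
| T2–T4 | 3 | 0.0167 | 2.441 | 65.7% | 0.69 |
| T1–T4 | 4 | 0.0125 | 2.550 | 61.7% | 0.72 |
| T0–T4 | 5 | 0.01 | 2.633 | 58.6% | 0.73 |

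**Step 3: the full Holm step-down.** The first step understates power, because later steps use a larger α. The complete procedure was therefore simulated with 40,000 runs per scenario, 45 per arm and d = 0.60 at post-intervention. The documents give neither the correlation between time-points nor the effects at other times. These are assumptions: correlation from 0 to 0.9, and three effect patterns.

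| Family | Effect at post-intervention only | Smaller effects at other times* | d = 0.60 at every post-baseline time in the family |
|---|---|---|---|
| T2–T4 (3 tests) | 66% | 66–69% | 72–75% |
| T1–T4 (4 tests) | 62% | 62–64% | 69–73% |
| T0–T4 (5 tests, no effect at T0) | 59% | 59–60% | 64–66% |

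*d = 0.3 at T1 (where it is in the family), 0.4 at T3 and 0.3 at T4.

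**Step 4: bound.** Holm can only make rejection harder than an uncorrected test at 0.05, so corrected power cannot exceed 80.4%. It would approach that value only if every other test in the family were almost certain to be rejected.

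**Step 5: what 80% would need at the first step.** With four tests n = 63.5, so 64 per arm; 64/0.8 = 80 per arm, or 160 in total. With five tests n = 66.6, so 67 per arm; 67/0.8 = 83.75, so 84 per arm, or 168 in total.

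**The case against.** The strongest reply is that the primary analysis is the mixed model and the t-tests are follow-up. A reader might infer from the shortfall that the trial is underpowered for its primary intention-to-treat analysis. The documents do not support that. They give no power for the mixed-model contrast, and a contrast that uses baseline can be more efficient. As an illustration, treat it as a change score with effect 0.60/√(2(1 − ρ)), where ρ is an assumed correlation with baseline, and test it at α = 0.0125. Power at 45 per arm is then 62%, 73% and 87% for ρ = 0.5, 0.6 and 0.7. At 56 per arm it is 74%, 84% and 94%. The primary contrast may or may not reach 80%. Sizing on a simple t-test in completers may also be what the authors meant by conservative. This part of the reply stands and limits the point to the post-hoc t-test. It does not remove the point, because the plan itself ties its 80% to that test.

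A second tempting inference starts from the per-protocol wording: with intention-to-treat primary, the effect should be diluted by 20% non-benefiting patients, to 0.60 × 0.8 = 0.48. The documents give no basis for this either. The 20% is a maximum drop-out rate, not a share of patients who are measured but gain nothing, and the Discussion separates non-adherence from drop-out.

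Third, the Holm family is not spelled out, so no single corrected figure can be given. That is fair, and it is why a range is reported. The correction also neither biases the estimate nor inflates type I error, and effect sizes with confidence intervals are planned in any case.

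**Conclusion.** The point holds for the post-hoc t-test on well-being at post-intervention. Its stated 80% power belongs to an uncorrected test, while the test planned is Holm-corrected. At d = 0.60 and 45 per arm, power is about 59–66% if all five time-points are in the family, 62–73% with the four post-baseline points and 66–75% with T2–T4 only. These ranges assume equal arms, a correlation between times of 0 to 0.9, and effects at other times no larger than 0.60. The direction does not depend on those assumptions, but the size does.

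The fault is a mismatch between the sizing and the analysis, not an error of arithmetic. It says nothing either way about the power of the primary mixed-model contrast. Two inconsistencies sit in the same passage: post-intervention is labelled T1 although Study design calls it T2, and the sample size is tied to the per-protocol analysis although the primary analyses are intention-to-treat.

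**What to change.** **Either** keep the correction over time-points. Define the Holm family explicitly and leave out T0, which precedes allocation. Restate the power for the corrected post-intervention test: with four tests, about 62% at the first step, or a detectable d of about 0.72 at 80% power. Remove the word *conservatively*. This changes wording only and needs no additional patients. The price is a lower stated power.

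**Or**, if the sponsor accepts that later time-points become secondary, prespecify the post-intervention contrast as the single confirmatory test at two-sided 0.05 without correction, and apply Holm to the rest. This also needs no extra patients, but it is more than wording: the Background states the primary aim as improvement in both the short and the long term, so that aim would have to be amended.

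**In both cases**, change the T1 label in the power section to T2, and state whether the power refers to the intention-to-treat or the per-protocol analysis. The choice should be made and recorded before outcome data are examined by arm, so that it cannot depend on whether the corrected or the uncorrected p-value is favourable.
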